## Methods/Design

### Hypotheses and design

Starting from current literature, we hypothesize that specific physical activity, WBV, may promote psychological wellbeing and quality of life in female aged subjects, if compared with Multicomponent Training program and normal physical activity. Therefore, we assume an improvement in proactive attitude, quality of life, wellbeing and happiness of WBV training group when compared to and Multicomponent Training and control group.

The comparison among WBV group, Multicomponent Training group and control group will be assessed in a three-arm randomized controlled clinical trial (Figure 1).

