### Measurements

Besides the psychological screening baseline at one week after the beginning of training (T1), all participants will be assessed at three months (T2) and six months (T3).Moreover, at the baseline assessment, questions on demographic variables (for example, age, marital status, work, educational level, socioeconomic status), psychiatric history (for example, previous diagnosis of depression and/or anxiety, family history regarding psychiatric diagnosis), and/or health behaviors (for example, alcohol use, smoking habits, physical activity) will be included.

All participating sample were screened for psychological aspects by the following standardized measures:

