#### *Primary outcome measures*

**SF-12 Health Survey** It is a self-administered test that assesses the global health status by the subjective point of view of the subject. It has been divided into two principal subscales: the Physical Component Summary (PCS) and the Mental Component Summary (MCS). In particular, it allows the assessment of concepts concerning health, physical functions, pain, general health, vitality, social functioning, emotional functioning and mental health [32].

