## Planned statistical analyses

The demographic and clinical characteristics of the three study groups will be compared at baseline to verify their homogeneity. To do this, analysis of variance (ANOVA) for continuous variables and chi-square test of Mantel-Haenszel test for discrete variables will be used. Complete and intent-to-treat analysis will be accomplished to compare primary outcome treatments. First, prevalence of happiness, proactive attitude, psychological wellbeing and quality of life will be displayed infrequency tables and both conditions (control and intervention)will be compared using the chi-square (Fisher’s exact test when appropriate) and Student’ s *t*-test, for discrete and continues variables respectively. The effect of the intervention will be determined using multilevel analyses (mixed effect regression models) to compare baseline and follow-up measures of all continuous data. In all these analyses a *P*-value of <0.05 will be considered statistically significant.

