## Sample size calculation

In this study, the change in scores in PGWBI and SF-12 are chosen as primary outcome measures to determine the effect of whole-body vibration approach. A difference of 0.5 standard deviations is considered necessary to find a clinically significant effect of the intervention. In order to detect this difference and assuming an 80% power, a minimum of 80 patients is needed in each outcome measure [36]. When assuming that 20% of participants dropout (quite a normal figure in this type of research), a minimum of 23 subjects per condition is needed to maintain sufficient power. We expect that in order to reach such a number, anticipating a response rate of 70% of which 20% is eligible, a total of 300 aged women will need to be screened.

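### One P<0.05 threshold covers all analyses, yet the joint primary scores, two WBV comparators and two visits have no lead test, order or success rule, so the primary error rate is left uncontrolled

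*Protocol article*

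**What the plan says.** All places are in the protocol article.

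- **Planned statistical analyses** closes with one rule for all the analyses it lists: a P-value "of <0.05 will be considered statistically significant". Neither sidedness nor any adjustment is given.
- **Sample size calculation** names two instruments jointly: "the change in scores in PGWBI and SF-12 are chosen as primary outcome measures".
- **Primary outcome measures** says of SF-12: "It has been divided into two principal subscales: the Physical Component Summary (PCS) and the Mental Component Summary (MCS"). With PGWBI this makes three candidate primary scores.
- **Hypotheses and design** describes a "three-arm randomized controlled clinical trial" and expects improvement in the "WBV training group when compared to and Multicomponent Training and control group". That is two WBV contrasts.
- **Measurements** states that "all participants will be assessed at three months (T2) and six months (T3"). Neither visit is called primary.

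No section ranks the scores, contrasts or visits, or says which combination of results would support the hypothesis.

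**The concern.** Several primary comparisons are possible and each would be judged at 0.05. Nothing in the text prevents one significant result among them from being reported as a positive primary finding. The chance of at least one such result when WBV has no effect is then well above 5%. The article wants the results to inform exercise and prevention programmes for older women, so a chance finding on one score, against one comparator, at one visit could be presented as the trial's answer.

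**Working it through.** The plan states no overall error rate, so there is none to reproduce. The calculation builds the possible primary families and finds the chance of at least one false positive in each.

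**Inputs from the article.** Per-test level 0.05, two instruments or three scores, two WBV contrasts, two post-baseline visits, equal allocation.

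**Derived.** With n per arm and common variance σ², each contrast of means has variance 2σ²/n. The two contrasts share the WBV arm, so their covariance is σ²/n and their correlation is (σ²/n)/(2σ²/n) = 0.5.

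**Assumed, because the article does not give them.** Two-sided tests, correlation between scores 0 to 0.7, correlation between visits 0.6.

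**Step 1, independence bound.** For m tests the risk is 1 − 0.95^m:
- 4 tests: 18.5%
- 6 tests: 26.5%
- 8 tests: 33.7%
- 12 tests: 46.0%

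**Step 2, correlated tests.** Multivariate normal test statistics were simulated under no effect anywhere (400,000 draws), each rejected beyond ±1.96. The three values in each cell are for score correlations 0 / 0.5 / 0.7.

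| Family (scores × contrasts × visits) | Tests | Any false positive, two-sided | Only errors favouring WBV |
|---|---|---|---|
| 2 × 2 × 1 | 4 | 17.3 / 16.2 / 14.9% | 8.9 / 8.1 / 7.5% |
| 3 × 2 × 1 | 6 | 24.8 / 22.0 / 19.2% | 13.1 / 11.1 / 9.6% |
| 2 × 2 × 2 | 8 | 28.8 / 27.0 / 24.8% | 15.0 / 13.6 / 12.5% |
| 3 × 2 × 2 | 12 | 39.8 / 35.6 / 31.5% | 21.6 / 18.3 / 15.9% |

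If score and visit correlations both range from 0 to 0.8, the 12-test risk is 25.6-43.7%.

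**Step 3, other readings of success.**
- *One overall test per score*, for example from one mixed model each: at most about 1 − 0.95² = 9.8% for two scores and 1 − 0.95³ = 14.3% for three.
- *WBV must beat both comparators on the same score and visit, any score sufficing:* about 0.9-2.5% in WBV's favour when no arm differs. If one comparator is truly worse, that contrast gives no protection. At score correlation 0.5 the two-sided risk is then 9.0% (two scores, one visit) to 21.2% (three scores, two visits), or 4.5-10.7% counting only errors favouring WBV.
- *WBV must beat both comparators on every primary score:* no inflation, because all tests must succeed together.

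**Step 4, power for the fix.** With a 0.5 SD difference and a two-sided t-test at 0.05, power is 88% with 80 evaluable per arm, 80% with 64 and 38% with 23. The stated 80 can be read as a per-arm number that already allows for dropout (64/0.8 = 80), but the article does not call it per arm. The 23 per condition does not follow from it, since 80/0.8 = 100. For Holm over six tests the first step is at 0.05/6 = 0.0083, where power is 69% with 80 per arm and 56% with 64.

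**The case against.** The strongest reply is that this is a condensed article. A multiplicity procedure is commonly left to an analysis plan, and an adjusted P-value can also be judged at 0.05. That is fair as far as it goes: the text does not exclude adjustment. But it sets one threshold for all analyses beside jointly named, unranked primary outcomes. Followed as written, that does not control the primary error rate.

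A reader might infer that the protocol plans twelve separate tests and that its false-positive risk is therefore about 36% rather than 5%. The documents do not support that. The analysis section says the mixed models compare baseline with follow-up, which could mean one model per score. It does not spell out separate T2 and T3 tests. It speaks of two conditions and lists no pairwise contrasts. The hypothesis joins the two comparators with an *and*, so a claim may be meant to require both. It is also directional, and errors favouring WBV are about half the two-sided figures. The correlations are assumptions.

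These points rule out any single headline figure, but the gap remains. The article adopts none of the stricter readings, and most of those examined leave the risk above 5%.

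**Conclusion.** The point holds in conditional form: the stated threshold, combined with unranked primary scores, comparators and visits, does not hold the primary error rate at 5%. If any one significant primary test counts as success, the two-sided risk is about 15-17% for the smallest pairwise family and about 31-40% for the largest, under the score and visit correlations assumed above. With one overall test per score it is at most about 10-14%. Only a rule that WBV must beat both comparators on every primary score removes the inflation outright, and no such rule is stated. The conflict between 80 and 23 in the sample size section is a separate matter and does not affect the error rates.

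**What to change.** Before outcome data are seen:

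1. Name one primary time point (for example T3) and one lead primary score and contrast.
2. Test the remaining primary score and contrast pairs in a fixed order at two-sided 0.05, stopping at the first non-significant result. The order is for the sponsor to choose. The article does not rank PGWBI against SF-12 or one comparator against the other.
3. Label T2, the happiness and proactive attitude scales and all other tests as secondary, and report them with confidence intervals.

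This changes wording only. The cost is that later steps may not be formally tested, so the position of the contrast with Multicomponent Training matters: if placed early and not significant, it blocks everything after it. The first test keeps its unadjusted power, which is 88% only with 80 evaluable per arm and 80% with 64. The 80 and the 23 must be reconciled separately before either power can be claimed.

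Holm across the same pairs avoids choosing an order but costs power: over six tests, about 69% at its first step with 80 per arm.

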## Sample size calculation

In this study, the change in scores in PGWBI and SF-12 are chosen as primary outcome measures to determine the effect of whole-body vibration approach. A difference of 0.5 standard deviations is considered necessary to find a clinically significant effect of the intervention. In order to detect this difference and assuming an 80% power, a minimum of 80 patients is needed in each outcome measure [36]. When assuming that 20% of participants dropout (quite a normal figure in this type of research), a minimum of 23 subjects per condition is needed to maintain sufficient power. We expect that in order to reach such a number, anticipating a response rate of 70% of which 20% is eligible, a total of 300 aged women will need to be screened.

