**Methods/Design:**

A randomized controlled trial (N = 300) will assess the relative effectiveness of two different exercise programs (whole-body vibration and Multicomponent Training) for improving psychological wellbeing in older-aged women. The following outcomes will be assessed at three time points (that is, pre, post, and follow-up): psychological wellbeing, proactive attitude, quality of life, and happiness.

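### The minimum of 23 women per condition contradicts the plan's own minimum of 80 and gives roughly 31–38% power for 0.5 SD (two-sided, unadjusted), not 80%

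*Protocol article*

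**What the plan says.** The Sample size calculation section names the sizing endpoints: "the change in scores in PGWBI and SF-12 are chosen as primary outcome measures". It sets the target: "A difference of 0.5 standard deviations is considered necessary to find a clinically significant effect of the intervention". It then gives a first number: "assuming an 80% power, a minimum of 80 patients is needed in each outcome measure". The dropout assumption follows ("When assuming that 20% of participants dropout"), and the same sentence concludes that "a minimum of 23 subjects per condition is needed to maintain sufficient power". The section ends with recruitment: a 70% response rate, 20% of responders eligible, and 300 women to be screened to reach the required number.

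Two other places bear on this. Planned statistical analyses sets the significance level ("a *P*-value of <0.05 will be considered statistically significant") and does not say whether tests are one- or two-sided. The abstract, under Methods/Design, gives a trial size: "A randomized controlled trial (N = 300) will assess the relative effectiveness of two different exercise programs". Hypotheses and design describes three arms.

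**The concern.** Two adjacent sentences give incompatible minimum sizes for the same target. The second is presented as the first after allowing for dropout, yet it is smaller by a factor of about 3.5 (80/23). An allowance for losses divides by the retained fraction, so it cannot reduce a requirement. The 80 is also attached to each outcome measure, which is not a unit of sample size, so the reader cannot tell whether it means per arm or in total.

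What is at stake is the claim that the stated minimum keeps sufficient power. If recruitment stops at that minimum, the trial would more likely than not miss the difference that the plan itself calls clinically significant, and a null result would be hard to interpret.

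**Working it through.** **Inputs from the article.** Difference d = 0.5 SD, power 80%, stated minimum 80, dropout 20%, 23 per condition, 70% response, 20% eligible and 300 screened (all from Sample size calculation); significance level 0.05 (Planned statistical analyses); three arms (Hypotheses and design).

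**Assumptions.** Two-sided test, with one-sided shown as a variant; equal arms; unadjusted two-sample t-test; 0.5 SD taken as the between-arm difference in SD units of the analysed change score.

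**1. Does the 80 reproduce?** Normal approximation: n per arm = 2(z₀.₉₇₅ + z₀.₈₀)²/d² = 2(1.960 + 0.842)²/0.25 = 62.8, so 63. The t-test gives 63.8, so 64 evaluable per arm. Inflating for dropout: 64/(1 − 0.20) = 80. The 80 therefore reproduces exactly as the number to enrol per arm, with dropout already included. Three arms need 3 × 80 = 240.

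**2. Does the 23 reproduce?** No variant does:

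| Reading | Before dropout | After dropout (÷ 0.8) |
|---|---|---|
| Two-sided t-test, per arm | 64 | 80 |
| One-sided t-test, per arm | 51 | 64 |
| 80 taken as evaluable per arm | 80 | 100 |
| 80 taken as the total of two arms | 40 per arm | 50 |
| 80 taken as the total of three arms | 27 per arm | 34 |
| Paired or one-sample t, two-sided | 34 | 43 |
| Paired or one-sample t, one-sided | 27 | 34 |
| Three-group ANOVA (total 177–235) | 59–79 per arm | 74–99 |

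Every entry exceeds 23, even before dropout.

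**3. Power at the stated minimum, d = 0.5.** If 23 are enrolled, 23 × 0.8 = 18.4, about 18 evaluable.

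| Evaluable per arm | Two-sided | One-sided | Difference detectable with 80% power (two-sided) |
|---|---|---|---|
| 23 | 38% | 51% | 0.84 SD |
| 18 | 31% | 43% | 0.96 SD |
| 64 | 80% | 88% | 0.50 SD |
| 80 | 88% | 93% | – |

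**4. Could baseline adjustment rescue 23?** Adjusting for a baseline with correlation ρ multiplies the required n by 1 − ρ². Setting 63.8(1 − ρ²) = 23 gives ρ = √(1 − 23/63.8) = 0.80. For 18 evaluable, ρ = √(1 − 18/63.8) = 0.85. With an assumed ρ of 0.5–0.7, power is 39–53% at 18 per arm and 48–64% at 23. The article assumes no correlation.

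**5. The recruitment figure.** 300 × 0.70 × 0.20 = 42 women, or 14 per arm. Even 23 per arm needs 3 × 23 = 69. At the stated yield of 0.70 × 0.20 = 14%, the numbers to screen would be 69/0.14 ≈ 493, 240/0.14 ≈ 1,714 and 300/0.14 ≈ 2,143.

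**The case against.** The strongest reply is that the abstract's 300 is the real trial size. That would be 100 per arm, 80 evaluable after 20% dropout and about 88% power, which would make the 23 a stray figure. From this a reader might infer that the intended chain is 80 evaluable, 100 randomised per arm and 300 in total, and that the correction is purely editorial. The article does not support so firm a reading. The 80 already equals 64/0.8, so dividing it by 0.8 again may count dropout twice, and the match with 300 may be coincidence. The sample size section also uses 300 for women screened, not randomised. What stands is that the harm is conditional: the trial is badly underpowered only if the 23 (or the 42 from screening) governs enrolment.

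A second reply is that 31–38% rests on an unadjusted two-sided t-test, while the article plans mixed-effect regression and does not state sidedness. This is fair, and the figures should carry that label. It does not change the direction: one-sided power is 43–51%, and adjustment reaches 80% only at correlations the article never claims.

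It is also tempting to say that the 80 is itself wrong for 80% power. That is so only if 80 means evaluable women per arm or a total over arms. As an enrolled number per arm it is correct.

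**Conclusion.** The point holds. The step from 80 to 23 is an error on the page, and the claim that 23 per condition keeps sufficient power is wrong under every reading examined. With the article's own inputs, 80% power needs 64 evaluable and 80 enrolled women per arm, 240 in all. At 23 per condition, power is about 31–38%, less than half of what is claimed, and the detectable difference is about 0.84–0.96 SD, or 1.7 to 1.9 times the target. These figures assume a two-sided 5% unadjusted t-test.

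The document does not establish which size is actually intended. It supports at least four totals: 42 from the screening yield, 69 from 23 per condition, 240 from 80 per arm, and 300 from the abstract. The finding is therefore that the sizing statement is contradictory and its power claim unsupported, not that the trial will certainly be underpowered.

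**What to change.** 1. Remove the 23 and the statement that it keeps sufficient power.
2. Give the 80 per arm instead of per outcome measure, and say whether it is before or after dropout. Two chains are consistent: 64 evaluable, 80 randomised per arm and 240 in total, for 80% power; or, if 300 are to be randomised, 100 per arm, 80 evaluable and about 88% power. State the sidedness alongside.
3. Reconcile the 300 screened with the abstract's trial size of 300 and with the 14% yield.
4. If about 23 per arm is what is really planned, withdraw the 80% power claim. State about 31–38% power for 0.5 SD (two-sided, unadjusted) and a detectable difference of about 0.84–0.96 SD.

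**Cost.** This is a change of wording only if 240 to 300 women are already to be randomised, or if the lower power is disclosed. Otherwise, at the stated yield, about 1,714 to 2,143 women would have to be screened instead of 300, which is a substantial recruitment change. Restating the power is then the cheap option.

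### 300 is given both as the randomised trial size and as the number screened, and at the stated 70% and 20% rates 300 screened yields 42 women, short of the plan's own minimum of 69

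*Protocol article*

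**What the plan says.** The Methods/Design paragraph of the abstract states: "A randomized controlled trial (N = 300) will assess the relative effectiveness of two different exercise programs". There 300 is the size of the randomised trial.

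The Sample size calculation section uses the figure differently. It sets the target difference ("A difference of 0.5 standard deviations is considered necessary to find a clinically significant effect of the intervention") at 80% power and gives a first requirement: "a minimum of 80 patients is needed in each outcome measure". After a 20% dropout allowance it gives a second: "a minimum of 23 subjects per condition is needed to maintain sufficient power". It then says how many women must be screened to reach that second number: "anticipating a response rate of 70% of which 20% is eligible, a total of 300 aged women will need to be screened".

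Hypotheses and design sets three arms: whole-body vibration, Multicomponent Training and control. Randomization intends equal group sizes, although it and Planned statistical analyses both speak of two conditions.

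**The concern.** A count of women screened and a count of women randomised can be equal only if everyone screened responds and is eligible. The plan expects 14% (70% of 20%). No section of the article reconciles the two uses of 300.

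The recruitment sentence also fails on its own terms, because 300 screened does not produce the minimum per condition that it is meant to produce. A team that plans its recruitment around 300 would fall short of the plan's own minimum. A reader of the abstract would expect a trial about seven times as large as the screening figure supports (300/42 = 7.1).

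**Working it through.** **Inputs, all from the protocol article**
- Trial size in the abstract: 300.
- Number screened, response rate and eligible share of responders (Sample size calculation): 300, 70%, 20%.
- Minimum per condition (same section): 23.
- Dropout, effect and power (same section): 20%, 0.5 SD, 80%.
- Number of arms (Hypotheses and design): 3, with equal allocation intended (Randomization).
- Significance level (Planned statistical analyses): 0.05, sidedness not stated.

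**Step 1. Try to reproduce 300 as the screening number**

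Number to approach = number required / (response x eligible), with 0.70 x 0.20 = 0.14.

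| Reading | Required | Women needed |
|---|---|---|
| Three arms, both rates | 3 x 23 = 69 | 69/0.14 = 493 |
| Three arms, counting responders only | 69 | 69/0.20 = 345 |
| Two conditions, both rates | 2 x 23 = 46 | 46/0.14 = 329 |
| Two conditions, counting responders only | 46 | 46/0.20 = 230 |
| One condition, both rates | 23 | 23/0.14 = 164 |

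No reading returns 300. For three arms, 300 is too few either way. Among the readings that count more than one condition, it is enough only with two conditions and 300 women who have already responded.

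**Step 2. Yield of 300 screened**
- Both rates applied: 300 x 0.70 x 0.20 = 42, and 42/3 = 14 per arm. After 20% dropout: 14 x 0.8 = 11.2 per arm.
- 300 already responders: 300 x 0.20 = 60, and 60/3 = 20 per arm.
- Plan's minimum: 23 per arm, 69 in all. Both yields are below it.

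**Step 3. Number to approach if the abstract's 300 is the number randomised**

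300/0.14 = 2,143.

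**Step 4. Power at the resulting sizes**

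Assumptions: one pairwise comparison, difference of 0.5 SD, unadjusted two-sample t-test at 5%. Under these, 80% power two-sided needs 64 per arm.

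| Per arm | Two-sided | One-sided |
|---|---|---|
| 14 | 25% | 36% |
| 11.2 (14 less 20% dropout) | 20% | 31% |
| 20 | 34% | 46% |
| 23 | 38% | 51% |

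**The case against.** **The sentence may have been written for two conditions.** Two sections do speak of both conditions. With two groups and 300 women who have already responded, 230 would be enough and 300 would cover it. This may explain where the figure came from. It does not rescue it, because Hypotheses and design sets three arms and the abstract would still give 300 as the trial size.

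**300 is a forecast, not a stopping rule.** This stands. The text says what screening effort is expected, and nothing says that recruitment ends at 300. A reader might infer that the trial will finish with 14 women per arm; the document does not say so. What is established is that the forecast does not match its own rates and target.

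**The power figures depend on choices the article does not make.** This also stands. Sidedness is not stated, and the planned mixed models use baseline data. If baseline adjustment removed variance at an assumed correlation of 0.5 to 0.7, power with 14 per arm would be about 31% to 43% two-sided. That is still far below 80%, but 20% to 25% is conditional on an unadjusted two-sided test.

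**The requirement might be read as 240.** A reader might take the 80 as per arm, giving 3 x 80 = 240 and 240/0.14 = 1,714 to approach. That reading would even produce the abstract's figure, since 240/0.8 = 300. But the section attaches 80 to each outcome measure and never says per arm, so 240 and 1,714 are inferences. The point does not need them, because 42 is also below 80 read as a total.

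**Conclusion.** The point holds. The same figure is used for two quantities that, on the plan's own rates, differ by a factor of 1/0.14, about seven. The screening forecast also misses its own target: 42 women against 69 (14 against 23 per arm), or 60 against 69 on the more generous reading.

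The 42 and 60 rest only on stated figures; the per-arm numbers add equal allocation over three arms. If recruitment did stop at 300 screened, the trial would be badly underpowered for the difference it calls clinically significant.

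The document does not show which of the two uses of 300 was intended. It would go too far to conclude that the abstract is the wrong one, or that 100 per arm is the planned size, a figure the article never states.

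**What to change.** 1. Settle the number randomised first. State it in total and per arm for three arms, identically in the abstract and in Sample size calculation. This requires saying what the 80 counts and how it leads to 23 per condition: a 20% dropout allowance raises a requirement (80/0.8 = 100) and cannot turn 80 into 23.
2. Then derive the number to approach as N/0.14 and label it as a separate quantity. At the stated rates this is about 493 for 69 randomised, or about 2,143 for 300 randomised. Say whether screened means approached or already responded.
3. If only 300 women will be screened, correct the abstract to about 42 randomised, acknowledge that this is below the stated minimum per condition, and replace the 80% power with the power that size gives, naming the test and sidedness. Under the t-test assumptions above this is about 25%, or about 20% after dropout.

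The edit to the text is small, but the consequence is more than wording. Either the recruitment effort rises well above 300 women, which bears on feasibility, or the stated power falls.
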